### Setting

The study will be conducted in an adult male prison in North-West England, UK, where the BFO program is not currently delivered as a standard treatment. This prison is a ‘Category D’ open prison where offenders are, subject to approval, provided with ‘Release on Temporary License’ (ROTL) where they are granted release to work in the community or have ‘home leave’. This prison is a resettlement prison which has an operational capacity of just over 600 male offenders, approximately a quarter of whom are either on life sentences or subject to indeterminate sentences. Approximately, 75% of the men in the prison are serving sentences of 4-years or longer at any one time. Around three-quarters of the men in the prison are over the age of 30 years, and around 40% have identified substance misuse difficulties. The prison places a strong emphasis on rehabilitation and community reintegration, running a range of vocational training courses, alongside initiatives to support the men serving sentences in the prison to maintain and enhance the relationships they have with their families.

This category of prison has been chosen for the study because, although even the very highest security prisons in the UK have significant issues with drug and alcohol use, offenders in a Category D prison may potentially have the most opportunity to use substances, as they spend some of their time in the community. Most participants may be on ROTL during the study, including resettlement day release, and resettlement overnight release, so it is more likely that outcomes related to substance use will be an artifact of treatment effects, rather than lack of opportunity to use substances due to incarceration in a highly secure environment. Although it is anticipated that most, if not all, participants will be receiving ROTL during the study, the ROTL status of each participant will be recorded during their first treatment session and this will be taken into account during data analyses, if there are a significant number of participants not provided with ROTL during the study. Participants will be recruited from standard alcohol and drug misuse services in the prison, which are delivered in coordination with Her Majesty’s Prison and Probation Service (HMPPS).

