### Participants

Participants included in the study will be offenders currently serving a prison sentence aged 18 to 65 years with problem alcohol and/or drug use of duration of 12-months or longer. This period of time is in line with DSM-V criteria for substance related disorders (American Psychiatric Association 2000). It is estimated that a total of 240 participants will need to be recruited and screened in order to obtain a sample of 120 evaluable participants (see ‘Power Calculation’).Inclusion criteriaMale offenders currently serving a prison sentence with problem alcohol and/or drug use aged 18 to 65 years.Willing and able to give informed consent for participation in the study.Has at least 3-months left to serve of their sentence at the prison acting as the research site, at the time they are recruited to the study.Problem alcohol and/or drug use present for at least 12-months prior to current prison sentence.Willing to follow treatment for problem alcohol and/or drug use for 4-weeks.Willing to provide outcome measures at 3- and 6-months follow-up.Concomitant alcohol and drug/s use permitted, as well as any prescribed medication.Exclusion CriteriaParticipation in any other alcohol and/or drug related clinical studies.Individuals detained under the Mental Health Act.Individuals with a known and diagnosed intellectual or developmental disability.Non-English speaking offenders (study information material and program only produced in English).

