The Informed Consent Form will be signed and dated by both the participant and the site investigator, and the participant’s preferred mode of contact (e.g. telephone, email etc.) and contact details for the completion of follow-up assessments will also be noted at this point. The participant will be provided with a copy of the signed consent form and the Participant Information Sheet. The original consent forms will be retained in a secure storage facility separately from source data to protect against breach of privacy and participant anonymity.

If written consent is given, each participant will then be screened for eligibility by the site investigator before then being randomized to either the BFO or control group. Randomization will occur at the level of the individual participants, with participants being assigned to one of the study groups following the generation of a random allocation sequence via the *Research Randomizer* (from the Social Psychology Network- Urbaniak and Plous 2011). Sequentially-numbered opaque sealed envelopes containing the treatment group that the participant will be allocated to will be delivered to the research site prior to commencement of the study. The participant number will be determined according to the order of enrolment in the study. The site investigator will assign and open one sealed envelope per participant. A screening log, including the participant number and treatment group assigned by randomization and any subsequent reason/s for exclusion from the study (if applicable), will then be completed by the site investigator.

No longer than 2-weeks after being randomized and completing the eligibility screening, both study groups will complete a battery of assessments to collect data around primary and secondary outcomes and demographic information including age and ethnicity. This battery of assessment will be delivered digitally via desktop computers within the prison IT suites. The assessment for the BFO group will be completed within the BFO program. The control group will complete the measures via a specially developed digital assessment platform which will deliver the same assessment that is included in the BFO program, but without providing access to any of the digital intervention content provided by BFO.

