### Data analysis

Quantitative data will be analyzed and reported using SPSS® Version 25.0 (or later) with all analyses to be performed as per the statistical analysis plan. The appropriate 95% - confidence interval will be applied. The *all-randomized population* will consist of all participants in the study that have been screened and allocated to either the i) BFO plus standard treatment, or, ii) standard treatment only group. The *per-protocol population* will consist of all participants randomized into the study who have completed the 4-week treatment period as well as all follow-up assessments.

Analyses will be performed on the basis of an ITT population, with the all-randomized population included in the analyses. No participants will be excluded from the ITT analyses, i.e. those who have withdrawn, been lost to follow-up, or have provided incomplete outcomes data. Separate analyses will also be conducted on the per-protocol population who have provided at least one set of follow-up data. Outcomes from these two analyses (ITT, per-protocol population) will be compared to examine whether missing data may have had an impact on reliability of conclusions formed around comparative effectiveness of the two study conditions.

Previous analyses (e.g. Elison et al. 2015a, b, c) indicate that data will likely be non-normally distributed in which case nonparametric repeated-measures analyses of covariance (ANCOVA) using appropriate distribution such as Poisson distribution, will be used to compare the study groups at 4-weeks post-treatment and 3- and 6-months follow-up on self-reported substance use, substance dependence, mental health sequelae, biopsychosocial functioning and quality of life. However, normality will be tested when data are available for analyses, and appropriate distributions will be applied.

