Specialist statistical support has been sought from colleagues at one of the collaborating academic institutions (University of Manchester), who have provided advice during protocol development and will provide ongoing advice throughout the study. When analyzing differences between the two study groups at each of the outcomes data time-points, (4-weeks post-treatment, 3- and 6-month follow-ups) baseline scores will be controlled for as post-treatment between-group differences may reflect both treatment effects and also group differences at baseline that randomization may not have addressed. Differences between the groups in post-treatment scores will be ascertained using estimated marginal means.

Effect sizes will also be calculated to examine robustness of between-group differences and within-group changes over time, using partial eta squared (ὴ^2^), which is an appropriate measure of effect size for ANCOVA. The numbers of participants fulfilling clinical threshold scores for substance dependence, depression and anxiety at baseline and post-treatment will also be examined.

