### Power calculation

Since the study is a parallel-group comparison, equal numbers of participants will be required for each of the groups; i) BFO plus standard treatment, and, ii) standard treatment only. The study projection of the sample size will require 60 evaluable participants in each treatment group to achieve enough power (assuming power of 0.80 with α = .05) with an allowance of 50% attrition at 3- and 6-months follow-up, which is in line with previous studies with offender populations receiving interventions for substance misuse in correctional settings (e.g. Crisanti et al. 2014). In addition, this level of attrition is also seen in substance misuse intervention research more generally (e.g. Brorson et al. 2013) and in many digital interventions studies (e.g. Eysenbach 2005). To obtain a total of 120 evaluable participants, it is estimated 240 participants will need to be recruited and screened.

These estimations have been based on previous samples used for assessments of CAT (Carroll et al. 2008), some of which have used longitudinal statistical analyses (Koski-Jännes et al. 2009; Kypri et al. 2008). It is envisaged that the estimated evaluable participant population will be sufficiently large to enable meaningful descriptive comparisons to be performed.

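### Problem class (alcohol, drugs or both) is not among the covariates the article names; adding it to the substance use and dependence models would buy some precision at almost no cost

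*Protocol article*

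**What the plan says.** **Population.** The Participants section of the protocol article admits men with "problem alcohol and/or drug use of duration of 12-months or longer". Alcohol-only, drug-only and mixed problem users form one sample.

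**Allocation.** Under Procedure, "Randomization will occur at the level of the individual participants", and participants are "assigned to one of the study groups following the generation of a random allocation sequence". The results sit in sequentially numbered sealed envelopes, used in order of enrolment. No stratification factor is described. Eligibility is checked before the envelope is opened. The assessment battery follows up to two weeks after randomisation.

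**Outcome.** Under Measures, the primary outcome combines quantity on a typical day, in a unit that depends on the substance, with days of use in a typical week. Weekly use before the current sentence is also asked.

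**Model.** Data analysis foresees "nonparametric repeated-measures analyses of covariance (ANCOVA) using appropriate distribution such as Poisson distribution" if the data are non-normal. The covariate rule for every outcome and time point is that "baseline scores will be controlled for as post-treatment between-group differences may reflect both treatment effects and also group differences at baseline". The Setting section adds one conditional factor, release on temporary licence (ROTL): "this will be taken into account during data analyses, if there are a significant number of participants not provided with ROTL during the study".

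**Size.** Power calculation asks for 60 evaluable men per group at 80% power and α = .05, with 50% attrition allowed for at 3 and 6 months.

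**The concern.** The article adjusts because randomisation may leave the groups different at baseline. One obvious candidate for such a difference is the kind of substance problem a man has. It is close to the eligibility criterion itself, and it determines the unit in which his primary outcome is counted. Yet it is not named as a covariate.

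The baseline score covers part of this, but perhaps not all. It is taken in custody, where use may be lower than before the sentence or after release. A man reporting little or no use at baseline reveals little about his substance. If outcomes differ by substance, the unexplained part widens the confidence interval, and an uneven mix between groups moves the estimate in that particular trial. At stake is efficiency in a small trial with heavy expected attrition.

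**Working it through.** **1. The plan's own figures.** Recruitment reproduces: 120 / (1 − 0.5) = 240. The 60 per group cannot be reproduced, because no effect size or SD is stated. Solved backwards (two-sided, normal approximation), it corresponds to d = (1.960 + 0.842) × √(2/60) = 0.51. That value is used below only as a reference point.

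**2. Chance imbalance.** Inputs: 60 per group from the Power calculation section, or 30 per group if the 50% attrition falls after the 4-week assessment. The article can be read either way. The share of men in one substance category is not given; the assumed range is 20% to 50%. The SD of the between-group difference in share is √(2p(1−p)/n), which for p = 0.5 is 0.091 at n = 60 and 0.129 at n = 30. Exact hypergeometric probabilities are:

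| Per group | Difference ≥ 10 points | Difference ≥ 20 points |
|---|---|---|
| 60 | 0.25 to 0.36 | 0.01 to 0.04 |
| 30 | 0.33 to 0.44 | 0.10 to 0.20 |

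For p = 0.5 and 10 points, the plain normal approximation gives 0.27 at 60 and 0.44 at 30.

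**3. What an imbalance does.** With two equal classes explaining a share R² of the variance left after baseline adjustment, class means differ by 2√R² residual SDs. A 10-point imbalance moves the estimate by 0.1 × 2√R²: 0.03 SD at R² = 2%, 0.06 at 10% and 0.09 at 20%. The standard error at 60 per group is √(2/60) = 0.18 SD. The shift is visible but well inside sampling error.

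**4. How much the baseline score already absorbs.** Suppose class accounts for a share b of total variance (set to 1), equally at baseline and follow-up, and the within-class correlation is r. Residual variance is 1 − (b + (1−b)r)² with the baseline score alone, and (1−b)(1−r²) with class added.

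- b = 0.1, r = 0.7: 0.467 falls to 0.459, a cut of 1.7%.
- b = 0.2, r = 0.5: 0.640 falls to 0.600, a cut of 6.3%.
- b = 0.4, r = 0.3: 0.664 falls to 0.546, a cut of 17.7%.

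Over b = 0.1 to 0.4 and r = 0.3 to 0.7, the further cut is about 2% to 18%.

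**5. Gain in power.** Power = Φ(2.802/√(1−R²) − 1.960) at 60 per group, and the number needed for 80% power is 60 × (1−R²):

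| Further R² (assumed) | Power | Per group for 80% |
|---|---|---|
| 2% | 0.81 | 59 |
| 5% | 0.82 | 57 |
| 10% | 0.84 | 54 |
| 20% | 0.88 | 48 |

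**6. Type I error.** t-tests at 60 per group, ignoring class, were simulated with 0%, 20% and 40% of variance between classes. They rejected a true null in 5.0% of trials each time.

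**The case against.** The strongest reply is that this reports silence. The article defers to a statistical analysis plan that is not shown, and covariates beyond the baseline score commonly belong there. The ROTL clause shows that the baseline sentence is not a complete covariate list even within the article. This stands: it can be said only that the article names no substance factor, not that the trial will lack one.

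Three stronger readings are tempting and are not supported.

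- **The between-substance variance stays whole in every comparison.** It does not, because the baseline adjustment removes part of it (step 4). For the PHQ-4, quality of life and RPM scores, the article gives no reason to expect a difference by substance.
- **The problem class is already recorded before allocation.** The article does not say so. Eligibility needs only an alcohol and/or drug problem, and the substance-specific questions come after randomisation. No variable for main problem substance is defined.
- **The omission biases the comparison or inflates type I error.** Randomisation protects the comparison on average, and ordinary standard errors already allow for random imbalance. A Poisson model with model-based standard errors is a possible exception. In simulations with class means of 6 versus 12 or 18 (assumed), it rejected a true null well above 5% when class was left out. A robust variance brought this back to about 5% to 7%. That is over-dispersion, a matter of how standard errors are computed, and the article does not fix this.

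It is also fair that an open prison was chosen because men there have opportunity to use. Low baseline use is therefore a possibility and not a stated fact. The floor effect in the Discussion concerns biopsychosocial functioning.

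**Conclusion.** The point holds as a minor efficiency recommendation. The article pools the problem classes, describes one unstratified sequence, and names only the baseline score for all comparisons. Some between-substance variance and chance imbalance is likely to remain after that adjustment, mainly for substance use and dependence.

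The size rests on assumptions throughout. If class explains a further 2% to 20% of residual variance, 80% power becomes about 81% to 88%. The model in step 4 suggests 2% to 18%, so the top of the range is generous. A 10-point imbalance has roughly a one-in-four to one-in-three chance at 60 per group and would move the estimate by less than half a standard error. Nothing in the article is stated wrongly or contradicted on this point.

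**What to change.** Note the problem class (alcohol, drugs, both) on the screening log when eligibility is checked, before the envelope is opened. Alternatively, derive it by a written rule from the questions on use before the current sentence. Pre-specify it as a fixed factor alongside the baseline score in the substance use and dependence models. The three-level class follows the eligibility wording, so mixed users need no further rule when it is noted at screening.

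The cost is one recorded item and two degrees of freedom. If the analysis plan already contains such a factor, a sentence in the article's Data analysis section would settle the matter.

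Stratified envelope lists are optional. Separate lists without blocking would not assure balance, so stratifying helps only if blocks are used within each class. A class factor does not make quantities of different substances comparable; that is a separate problem with the primary outcome and needs its own solution.

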### Power calculation

Since the study is a parallel-group comparison, equal numbers of participants will be required for each of the groups; i) BFO plus standard treatment, and, ii) standard treatment only. The study projection of the sample size will require 60 evaluable participants in each treatment group to achieve enough power (assuming power of 0.80 with α = .05) with an allowance of 50% attrition at 3- and 6-months follow-up, which is in line with previous studies with offender populations receiving interventions for substance misuse in correctional settings (e.g. Crisanti et al. 2014). In addition, this level of attrition is also seen in substance misuse intervention research more generally (e.g. Brorson et al. 2013) and in many digital interventions studies (e.g. Eysenbach 2005). To obtain a total of 120 evaluable participants, it is estimated 240 participants will need to be recruited and screened.

These estimations have been based on previous samples used for assessments of CAT (Carroll et al. 2008), some of which have used longitudinal statistical analyses (Koski-Jännes et al. 2009; Kypri et al. 2008). It is envisaged that the estimated evaluable participant population will be sufficiently large to enable meaningful descriptive comparisons to be performed.

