Study groups will then complete a period of 4-weeks of substance misuse treatment, of either i) BFO plus standard treatment, or ii) standard treatment only. For the BFO group, the 4-week intervention will be delivered to groups of approximately 10 participants at a time, so it is estimated that approximately 6–8 groups will need to run successively to achieve the sample size required, in order to account for some attrition between baseline and 4-week post-treatment assessments. BFO group participants will receive two sessions of BFO each week, alongside any standard treatment they may be engaging with.

Online access to the BFO program is granted via the activation of an access code given to the participant at the alcohol and drug misuse service by authorized practitioners. To activate the access card and create a personal account, the participant must enter a username and password of his choice along with the access code. The practitioners will be able to assist with the online access if required. The participants must also agree to the Terms & Conditions of using BFO, which are in accordance with the Participant Information Sheet and Informed Consent Form and conform to the European Union General Data Protection Regulation around the use of digitally captured personal data. The practitioners must ensure that they log out of BFO at the end of each treatment session to protect the confidentiality of the data.

Procedures to enhance retention of participants during the 4-week treatment period will include practitioners providing ongoing support during weekly key-working sessions, which all offenders in the prison will routinely receive during the standard substance misuse treatment. When participants do dropout of the study, new participants will be recruited and randomized to replace dropouts, in order to ensure the required sample size of 120 participants (60 per group) complete the 4-week treatment period and provide post-treatment data. However, in line with ITT principles, all randomized participants, including dropouts, will be included in the final analyses (see ‘Data Analysis’ section). After completion of the 4-week treatment period, participants in both groups will complete the same battery of digital psychometric assessments on the prison desktop computers.

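### The protocol contradicts itself on the sample size behind its 0.80 power: 60 per group is what remains after 50% follow-up attrition in one section, but 4-week completers before that attrition in another

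*Protocol article*

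**What the plan says.** Three sections of the protocol article give the sample size.

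- **Power calculation.** The requirement is "60 evaluable participants in each treatment group to achieve enough power (assuming power of 0.80 with α = .05) with an allowance of 50% attrition". The attrition meant is the loss by the two later follow-ups, 3 and 6 months after treatment. The section repeats that 120 evaluable men will be obtained from 240, attributes the estimate to the sizes of earlier studies, and ends by expecting a sample "sufficiently large to enable meaningful descriptive comparisons to be performed".
- **Participants.** The estimate is that "a total of 240 participants will need to be recruited and screened in order to obtain a sample of 120 evaluable participants".
- **Procedure.** Dropouts are replaced by newly randomized men "in order to ensure the required sample size of 120 participants (60 per group) complete the 4-week treatment period and provide post-treatment data". BFO is delivered to about 10 men at a time, and "approximately 6–8 groups will need to run successively to achieve the sample size required". The stated reason for that number of groups is attrition between baseline and the 4-week assessment. Follow-up attrition is not mentioned there.

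The Data analysis section compares the groups at 4 weeks, 3 months and 6 months, adjusts for baseline, and includes all randomized men. The article does not single out one of these time points as primary.

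**The concern.** The same figure, 120 men or 60 per group, sits at two different points in the participant flow. In the Power calculation it is the number left after half have been lost at follow-up. In the Procedure it is the number finishing 4 weeks of treatment, before that loss occurs. Both cannot be the number behind the 0.80.

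Two things are at stake. The first is practical: site staff cannot tell whether to randomize about 120–160 men and run 6–8 BFO groups, or to randomize 240 and run about 12. The second is interpretation: if the Procedure is followed and 60 per group really is what 80% power requires, two of the three between-group comparisons are made with clearly less power than the article states.

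**Working it through.** **Inputs from the protocol.** Power 0.80, α = .05, 60 evaluable per group, equal groups, 50% attrition at 3 and 6 months, 240 recruited and screened (Power calculation, Participants); 60 per group secured at 4 weeks, 6–8 BFO groups of about 10 (Procedure).

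**Assumptions made here.** A two-sided test (sidedness is not stated), a normal approximation for comparing two means, no covariate adjustment, and complete cases only. The article gives no effect size, so the 0.80 itself cannot be reproduced. The standardized difference d is back-solved from 60 per group.

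**Step 1: reproduce the 240.** 120/(1 − 0.50) = 240. This matches exactly, so the Power calculation places 120 after the 50% loss.

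**Step 2: what the Procedure delivers.**
- BFO men: 6 × 10 = 60 to 8 × 10 = 80.
- Randomized with equal allocation: 2 × 60 = 120 to 2 × 80 = 160.
- Remaining per group after 50% loss: 60 × 0.5 = 30 to 80 × 0.5 = 40. The lower figure applies when half of the 60 completers are lost. The upper applies when all 80 places are filled and half of those men are lost.
- For comparison, 240 randomized puts 120 men in the BFO arm, and 120/10 = 12 groups.

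**Step 3: power at the smaller number, if 60 per group gives 80%.** With n per group, power = Φ[(1.960 + 0.842) × √(n/60) − 1.960]. The effect size and the outcome's SD cancel out.
- n = 40: 2.802 × 0.816 − 1.960 = 0.328, power 63%.
- n = 30: 2.802 × 0.707 − 1.960 = 0.021, power 51%.

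The exact t-test gives 62% and 50%. A one-sided test gives 65% and 55%.

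**Step 4: detectable difference at 80% power.** d = 2.802 × √(2/n):

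| n per group | detectable d |
|---|---|
| 60 | 0.51 |
| 40 | 0.63 |
| 30 | 0.72 |

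The t-test gives 0.52 at n = 60 and 0.74 at n = 30.

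**Step 5: power over an assumed range of effects.**

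| d | n = 30 | n = 40 | n = 60 |
|---|---|---|---|
| 0.3 | 21% | 27% | 38% |
| 0.4 | 34% | 43% | 59% |
| 0.5 | 49% | 61% | 78% |
| 0.6 | 64% | 77% | 91% |
| 0.7 | 77% | 88% | 97% |

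**Step 6: baseline adjustment.** With a baseline correlation r, the detectable d is multiplied by √(1 − r²) at every n. At r = 0.5 it becomes 0.44 for 60 per group and 0.63 for 30. The ratio between the two stays at √2, so adjustment improves both figures without closing the gap.

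**The case against.** The strongest reply is that the sections can be read as consistent. On this reading, 60 per group at 4 weeks is already large enough to tolerate losing half later, and the 240 are men consented and screened before randomization, which is the order the Procedure gives. The chain is then 240 screened, about 120–160 randomized, 120 completing 4 weeks and about 60–80 followed up. Six to eight BFO groups suffice, and 80% power at follow-up with 30 per group implies d of about 0.72. At that effect, 60 per group gives about 98% power at 4 weeks.

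This reading is possible, and it is why the 50–63% must stay conditional. Its cost is that the 240 no longer follows from the stated attrition, although 120/0.5 reproduces it exactly. The single 50% would be spent before randomization, and the article gives no screening-failure rate to support that. The wording still has to be reconciled.

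Other limits also stand. The planned analysis is baseline-adjusted, repeated-measures and on all randomized men, so it may recover some of the information lost, and the unadjusted t-test figures are not the trial's own power. At 4 weeks the Procedure does secure 60 per group. The Discussion openly lists attrition as a limitation.

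A reader might be tempted to go further in four ways that the document does not support:
- **That the trial has only even odds of detecting its own target effect.** No target effect is stated in the article; d of about 0.51 is back-solved here.
- **That exactly 30 per group will remain.** The plan implies 30–40.
- **That replacing dropouts invalidates the comparison.** All randomized men, including dropouts, stay in the analysis, so a fixed number to randomize is largely a design preference.
- **That the missing effect size is itself an error.** It may be in the statistical analysis plan, and this point does not rely on its absence.

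**Conclusion.** The contradiction is real and lies within the article. Participants and Power calculation derive 240 from 120 men remaining after 50% attrition. Procedure makes the same 120 the 4-week completers, replaces dropouts only up to that point, and provides 60–80 BFO places where 240 randomized would need 120. Under the protocol's own attrition, the stated size and the stated power cannot both hold at 3 and 6 months if 60 per group is what 80% power requires.

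The size of the shortfall on that reading is 30–40 per group and power of about 50–63% at two of the three time points, or a detectable difference larger by a factor of 1.2 to 1.4 (√(60/40) to √(60/30)). This rests on a two-sided, unadjusted, complete-case approximation. The 4-week comparison is not affected. It is not established that the trial is underpowered, because the article does not fix which reading is meant.

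**What to change.** 1. State at which time point 60 per group must be evaluable, and whether 240 counts men screened or men randomized.
2. Give one chain of numbers (screened, randomized per group, completing 4 weeks, assessed at 3 and 6 months) and use it in Participants, Procedure and Power calculation.
3. Then choose one of two routes:
   - **Keep 60 per group at 4 weeks.** Limit the 0.80 to that time point, drop the statement that it allows for 50% follow-up attrition, and give the lower power, or the larger detectable effect, at 3 and 6 months. Calculate it for the assumed effect size and the planned baseline-adjusted analysis; the figures above show the scale and should not be copied in as the trial's own.
   - **Keep 60 per group after follow-up loss.** Make the number randomized 240 and the number of BFO groups about 12.

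The first route costs rewording and a less favourable follow-up power figure, with no extra enrolment. The second is a real expansion: run one after another, 12 groups of 4 weeks take 48 weeks, against 24–32 weeks for 6–8 groups, before the last 6-month follow-up in a study expected to last about 18 months.
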